## 8 IMMUNOLOGIC MONITORING AND STATISTICAL ANALYSIS

Immunological response evaluations for baseline values will be conducted on the pre-vaccine leukapheresis sample. An additional leukapheresis will be required for any patients who have a positive DTH skin test for PEPvIII for immunologic monitoring. Immunologic response evaluations will also be performed from peripheral blood obtained. A comparison of pre-therapy lymphocyte functions to those at intervals after each immunization and subsequently will be made. These tests may provide evidence for the inhibition of  $T_{Reg}$  function or a change in the quantity or quality of immune responses following CDX-110 immunization and will play an important role in the design of future CDX-110-based clinical trials.

Clinical and immunologic endpoints will be analyzed in all patients and statistical considerations described below are powered based on enrollment of 20 patients. However, an analysis of patients stratified at enrollment based on complete resection or residual disease will be performed for hypothesis generation on the role of tumor burden on clinical and immunologic responses to PEPvIII vaccination and daclizumab.

### **8.1.1 Overview of Statistical Analysis**

Our laboratory and the HVTN Immunologic Monitoring Reference Laboratory, headed by [name] also at Duke University, has devoted considerable effort to co-developing and co-validating the immunologic assays outlined below for monitoring  $T_{Reg}$  function, antigen-specific responses in CD8+ or CD4+ T-cells, and NK cell functional activity in cancer patients. The reproducibility of these assays in our hands ensures that they can be reliably used for monitoring of changes after vaccination with and without daclizumab. Power calculations for this study are based on our primary endpoint which is functional suppressive capacity of CD4+CD25+CD127-  $T_{Regs}$ . For these calculations, we assumed that measurements made in each treatment group at a given phytohemagglutinin (PHA) level would be normally distributed with standard deviation of  $\sigma$ . Based on our experience with these assays within this patient population (Fecci, Mitchell et al. 2006), we estimate that with a sample size of 20 randomized patients we will have 80% power to detect a difference of 1.41  $\sigma$  at the 0.017 significance level (one-tailed). A 0.017 level of significance is used to adjust (Bonferroni correction) for the use of 3 non-zero PHA doses (0.1, 1, 10  $\mu$ g/well) in the proliferation assay. Thus, with only 20 patients, we will have sufficient power to detect treatment effects much more subtle than the ones observed in our pre-clinical studies (Fecci, Sweeney et al. 2006) and effects that we believe would be clinically significant. However, because the magnitude and variability of the effects of daclizumab on  $T_{Regs}$  remain unknown in humans, once human data become available from these studies, power analyses will be recalculated and patient numbers adjusted if needed. If daclizumab treatment does not significantly inhibit the functional recovery of  $T_{Regs}$  (primary endpoint), we would not be interested in the further development of this drug as

a vaccine adjuvant. Therefore, a one-sided hypothesis test is utilized. Power calculations are not provided for subsequent analyses as the number of patients in this trial will be determined by the primary endpoint, and the remainder of the analyses is exploratory and hypothesis generating only. With 10 patients in each arm, however, we will have 80% power to detect difference  $>1.325\sigma$  between groups for each assay at  $\alpha=0.05$ .

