## 5 INVESTIGATIONAL PLAN

### 5.1 Preparation and Administration of Therapeutic Agents

#### 5.1.1 Overview

Twenty patients with newly-diagnosed EGFRvIII+ high grade glioma will undergo leukapheresis for immunologic monitoring. Only 1 dose level of daclizumab (1 mg/kg) will be assessed. The decision to dose escalate in subsequent trials will be dependent on analysis of the safety and immunologic responses obtained in this trial. Patients will be followed until death. This study will be halted if any 2 patients experience a drug-related Grade IV or irreversible Grade III toxicity. After initial leukapheresis, all patients will then receive RT and concurrent TMZ at a standard targeted dose of 75 mg/m^2/d. Patients with progressive disease during radiation, dependent on steroid supplements above physiologic levels at time of vaccination, unable to tolerate TMZ or whose PBLs fail to meet release criteria will be replaced, but no more than 40 patients will be enrolled overall. Remaining patients will then receive the initial cycle of TMZ at a targeted dose of 100mg/m^2/d for 21 days 3 ± 1 weeks after completing RT and will be independently randomized to receive daclizumab versus saline simultaneous with vaccine #1. An additional cohort of 6 patients (cohort #2) will receive serial administrations of daclizumab during vaccine # 1, vaccine # 3, and during the recovery from each TMZ cycle for the first 3 cycles at the same dose. Vaccines will be given intradermally and divided equally to both inguinal regions. The calculated dosage of daclizumab will be administered in a 50 mL of sterile 0.9% sodium chloride solution via a peripheral or central vein over a 15 minute period. Vaccine #2 and #3 will occur at 2 week intervals. Patients will then be treated monthly with TMZ cycles for a total of 6 cycles after RT. TMZ will be given on days 1-21 of a 28 day cycle. While standard dose 21-day TMZ treatment at 100 mg/m^2/day is recommended, the TMZ regimen may be adjusted at the discretion of the treating neuro-oncologist. Vaccine will always be given on day 21 ± 2 of each 28 day TMZ cycle. Subsequent vaccines will be given on day 21 ± 2 of each of the 5 remaining TMZ cycles. Cohort #2 will receive subsequent vaccinations along with daclizumab (1 mg/Kg) on day 21± 2 for first 3 cycles. Vaccines will then continue monthly until progression. An additional leukapheresis will be required for any patients who have a positive DTH skin test for PEPvIII for immunologic monitoring. Patients will be imaged after vaccine #4 and then bimonthly without receiving any other prescribed antitumor therapy until progression. Blood work for immunologic monitoring will be drawn before vaccine #1 and then monthly after vaccine #3. Blood work for sub-clinical autoimmunity will be drawn before vaccine #1 and every 4 months after vaccine #3. As part of standard care for these patients, upon tumor progression, participants may undergo stereotactic biopsy or resection. As this is not a research procedure consent will be obtained separately. However, if tissue is obtained, it will be used to confirm tumor progression histologically and to assess immunologic cell infiltration and EGFRvIII antigen escape at the tumor site.

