
### **8.2.1 Statistical Analysis**

Our primary endpoint analysis will consist of a comparison of proliferative T-cell response to PHA among treatment groups (+/- daclizumab) using a generalized linear model for normal data that accounts for correlation of measurement replication across PHA doses (0, 0.1, 1, 10  $\mu\text{g/well}$ ) within subjects. This analysis determines whether the difference in treatment groups relative to proliferative response remains constant over 4 PHA doses (i.e. curves remain parallel or not). A test of interaction with 3 degrees of freedom will be used. If the curves deviate significantly from parallelism, we will conclude that the effect of treatment varies as a function of PHA dose level. Within the

context of this model, statistical contrasts will be used to assess treatment differences at specific PHA dose levels. If the test for interaction is not statistically significant, one will conclude that the treatment effect is constant over PHA dose levels. A generalized linear model without an interaction will be used to assess whether the main effect for treatment is statistically significant (i.e. treatment differences are non-zero). In this analysis and others, if assumptions required for t-tests are not satisfied, a non-parametric Wilcoxon rank sum test will be conducted at each PHA level. Significance for this and other assays will be taken at the  $\alpha=0.05$  level unless otherwise indicated. A Bonferroni correction will be used to control for the multiple comparisons.

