## **9.3 Data and Safety Monitoring Plan**

This clinical research study will be monitored both internally by the PI and externally by the Duke University Medical Center Cancer Center's Protocol Review and Monitoring system in accord with their NCI-approved "Institutional Protocol Monitoring Procedures and Guidelines for NIH-sponsored Research Involving Human Subjects." In terms of internal review the PI will continuously monitor and tabulate adverse events. Appropriate reporting to the Duke University Medical Center IRB will be made. If an

unexpected frequency of grade III or IV events occur, depending on their nature, action appropriate to the nature and frequency of these adverse events will be taken. This may require a protocol amendment, dose de-escalation, or potentially closure of the study. The PI of this study will also continuously monitor the conduct, data, and safety of this study to ensure that:

- Interim analyses occur as scheduled;
- Stopping rules for toxicity and/or response are met;
- Risk/benefit ratio is not altered to the detriment of the subjects;
- Appropriate internal monitoring of adverse events and outcomes is done;
- Over-accrual does not occur;
- Under-accrual is addressed with appropriate amendments or actions;
- Data are being appropriately collected in a reasonably timely manner.

External review of this protocol begins with an initial review by the CPC, which performs a risk assessment of the trial. The PI will abide by their assessment of the level of risk, which will determine the intensity of subsequent external monitoring. Documentation of this assessment will be maintained. A formal, independent audit will be conducted by the Scientific Monitoring Subcommittee of the CPC after the first 3 subjects are enrolled. Assuming a “satisfactory” review, thereafter, the Scientific Monitoring Subcommittee of the CPC will review selected patients enrolled on this protocol on a bi-annual basis. This includes review of aggregate toxicity as reported in the progress report, accrual, amendments, and outcomes. If there appears to be an unexpected frequency of serious and/or unexpected toxicity or other significant issues, a full re-audit will be initiated. Any rating less than satisfactory will also prompt a full re-audit and corrective plan.

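### Section 8.1.1 lets patient numbers change on the observed daclizumab effect without a rule, a maximum or an alpha provision; depending on the unstated rule, per-dose type I error runs from no inflation to about 0.03

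*Protocol*

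**What the plan says.** Protocol section 8.1.1 sizes the trial on regulatory T-cell suppressive function: 20 randomized patients, 10 per arm, 80% power for a difference of 1.41 SD. On alpha it states "A 0.017 level of significance is used to adjust (Bonferroni correction) for the use of 3 non-zero PHA doses" and, because only inhibition would justify further development, "Therefore, a one-sided hypothesis test is utilized".

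The same paragraph then opens the sample size to change. The reason is "because the magnitude and variability of the effects of daclizumab on" regulatory T-cells are not yet known in humans. The action is "once human data become available from these studies, power analyses will be recalculated and patient numbers adjusted if needed".

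Section 8.2.1 sets the final analysis: a dose-by-treatment interaction test, then dose-specific contrasts if it is significant, or a main-effect test if it is not. The level is 0.05 unless otherwise indicated. On error control it says "A Bonferroni correction will be used to control for the multiple comparisons".

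The only numerical ceiling is in sections 5.1.1 and 5.2.1 and the synopsis, in the sentence about replacing patients: "no more than 40 patients will be enrolled overall". Section 9.3 asks the principal investigator to ensure that "Interim analyses occur as scheduled", but the protocol contains no interim schedule.

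**The concern.** Changing N because of variability is harmless in practice. Changing it because of the observed treatment effect is not: the final statistic then reuses data that have already decided how much more data to collect, and its null distribution is no longer the one behind the 0.017 critical value. Section 8.1.1 names magnitude alongside variability, so it permits the second kind. The stated correction covers the three PHA doses only and does nothing for the adaptation.

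This is the primary endpoint. Section 8.1.1 says daclizumab would not be developed further as a vaccine adjuvant if it fails, so a false positive here carries the drug forward.

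**Working it through.** **Inputs from the protocol (8.1.1, 8.2.1).** 10 per arm; one-sided 0.017 per dose; 80% power; 1.41 SD; three non-zero PHA doses. **Assumed, because the protocol does not say:** a look at 5 or 10 per arm, a maximum of 20 per arm, normal data, and a dose correlation between 0 and 0.9.

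**1. The plan's own figure.** A two-sample t-test with 10 per arm at one-sided 0.017 has 79.7% power at 1.41 SD (noncentral t, 18 df). The figure reproduces.

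**2. What a recalculation from the observed effect does.** N per arm = 2 × [(z0.983 + z0.80) × SD / effect]² = 2 × (2.120 + 0.842)² × (SD/effect)² = 17.5 × (SD/effect)². The maximum of 20 is reached once the observed effect falls below √(17.5/20) = 0.94 SD. With no true effect, the standard error at 10 per arm is √(2/10) = 0.45 SD, so the trial would nearly always be extended.

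**3. Per-dose type I error with no true effect, nominal 0.017.**

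| Rule (none is in the protocol) | Error |
|---|---|
| No change in N | 0.017 |
| N reset from the SD only, not below 10 per arm | 0.017 to 0.018 |
| Extend only if the recalculated N fits under the maximum, otherwise keep 10 per arm | about 0.017 or below |
| One final test, N raised on the observed effect, 10 to 20 per arm | about 0.021 to 0.022 |
| Look at 5 per arm, N may fall or rise, at most 20 per arm | 0.029 |
| Test at 10 per arm, retest at 20 per arm if not significant | 0.029 |

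The last row also follows directly. The two z-statistics have correlation √(10/20) = 0.707, and 1 − P(Z1 < 2.120 and Z2 < 2.120) = 0.0288.

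**4. Least favourable choice of N.** Given the interim statistic z1 at n1 per arm, the conditional chance of rejecting at n per arm is 1 − Φ[(2.120√n − z1√n1)/√(n − n1)]. Taking the largest value over n and integrating over z1 gives 0.030 (look at 10 per arm, n from 10 to 20), 0.034 (look at 5 per arm, stopping there allowed) and 0.042 (look at 10 per arm, practically no maximum).

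**5. Family of three doses**, with all three t-tests always performed.
- No change in N: 0.034 to 0.050.
- One final test, N reset from the observed effect: 0.037 to 0.064 (0.037 to 0.046 if the mean effect over doses drives N).
- Test and retest: 0.084, 0.079, 0.074 and 0.059 at correlations 0, 0.3, 0.5 and 0.8; about 0.048 at 0.9 in a normal approximation.

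**6. Main-effect route (8.2.1).** If this is one one-sided test at 0.05, test and retest gives 0.080.

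**7. Check of the remedies.** Two equally spaced looks at a nominal 0.0098 each give 0.0169 overall. A fixed-weight inverse-normal combination test at 0.017 gives 0.017 per dose and 0.036 to 0.050 for the family.

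**The case against.** The protocol describes recalculating power and changing N. It does not describe a significance test at 20 patients followed by another at 40. A reader might infer 0.029 per dose and 0.07 to 0.08 for the family as the consequence of the clause. The documents do not support that: both figures need an uncorrected retest, and the second also needs a dose correlation of roughly 0.3 to 0.5, which is nowhere given. Measurements at different doses come from the same subject, so a higher correlation is plausible. The family figures also ignore the interaction gate and the main-effect route in 8.2.1. Nor is 0.029 a ceiling, as step 4 shows. This part of the objection stands.

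A reader might also take the 40-patient limit as a cap of 20 per arm. It counts enrolled patients, including those replaced before randomization. Section 10.1 expects 12 consented to yield 6 treated in cohort #2; at that ratio 40 enrolled would give 40 × 6/12 = 20 randomized, leaving no room to extend. The maximum of 20 per arm used above is therefore only an assumption. Likewise, the interim-analysis line in 9.3 is one item in a general monitoring list and does not show that an efficacy look is planned.

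Two further replies carry less weight. The phrase about these studies could mean later trials, but 8.1.1 goes on to say that the primary endpoint determines the number of patients in this trial. And operating details may sit in an analysis plan that is not shown. The point, however, is what the protocol itself authorizes: a change in size driven by the effect, beside an alpha set without regard to it.

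That this is an early-phase trial with a biomarker endpoint is a fair reason not to rate the point higher.

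**Conclusion.** The defect is real and modest. Section 8.1.1 permits patient numbers to follow the observed effect, with no rule, no maximum randomized number and no protection of the type I error. The one-sided per-dose error runs from no inflation, through about 0.021 to 0.022 for the mechanism closest to the wording (one final test, N raised to an assumed 20 per arm), to about 0.03 under test-and-retest or an early look with reduction allowed. Looser rules could exceed 0.03.

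Family-wise error can be given only as a range under stated assumptions: 0.037 to 0.064 with one final test, and 0.059 to 0.084 with test-and-retest for correlations from 0.8 down to 0. It would be wrong to say that family control is lost in general. That depends on the rule, the dose correlation and the route taken through 8.2.1.

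**What to change.** Replace the sentence in 8.1.1 with a rule on these lines:

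- Sample size may be re-estimated once, at a stated time, from the blinded pooled SD only, keeping the planned detectable difference in assay units.
- The number randomized is not reduced below 20. It has its own stated maximum, kept separate from the 40-enrolled replacement limit and reconciled with it.
- No arm comparison of the primary endpoint is made before the final analysis.

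If the sponsor wants to use the observed effect, pre-specify a combination test or an adjusted boundary instead. One example is Pocock, with a nominal 0.0098 at each of two equally spaced looks for an overall one-sided 0.017. Apply the same protection to the main-effect test in 8.2.1, at that test's own level.

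Point the interim-analysis line in 9.3 to this rule, or delete it.

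The cost is protocol wording. Under the blinded rule the trial cannot be enlarged merely because the observed effect is smaller than hoped. Under the alternative it pays a small penalty in the critical value.

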### **8.4 T-cell Cytokine Production**

CD4+ T-cells derived from patients in each group will be cultured in 96-well plates with 0, 5, or 10  $\mu$ g of PHA or PEPvIII or KLH. After 16 and 72 hours of culture, supernatants are harvested and processed in duplicate with a custom BioRad Bio-Plex 7-plex (IL-2, IL-4, IL-6, IL-10, IL-12 (p70), IFN- $\gamma$ , TNF- $\alpha$ ) Cytokine Reagent Kit (BioRad) to differentiate responses into TH1 and TH2 types. Briefly, supernatants are incubated with anti-cytokine conjugated beads, followed by incubation with biotinylated

detection antibody. Reaction mixture is detected with streptavidin-PE and analyzed on a Luminex 100 machine (Luminex Corporation, Austin, Texas). Unknown cytokine concentrations are calculated by BioPlex Manager software using standard curves derived from a recombinant cytokine standard. Commercial ELISAs will be used to measure IL-7, IL-15, and TGF- $\beta_{1-2}$  production as well.

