### **8.5.1 Statistical Analysis**

The analysis used here will be one that has been successful at distinguishing HIV progressors and non-progressors based on T-cell phenotype (Betts, Exley et al. 2005; Betts, Gray et al. 2006; Betts, Nason et al. 2006). All data will be background subtracted. For each measure, a lower threshold corresponding to 2SD above background is set to 0 based on a Poisson model essentially allowing T-cells to be designated as positive or negative for a certain phenotypic marker. The number of positive phenotypic markers post-vaccination will be calculated for each patient. Treatment groups (+/- daclizumab) will be compared relative to the number of phenotypic markers observed post-vaccination for each antigen using a Wilcoxon rank sum test. Additional exploratory analyses will be conducted using a Fisher's exact test that will compare treatment groups with respect to the proportion of patients with  $\geq 4$  positive markers. Correlations between phenotypic markers and EGFRvIII loss on recurrence will also be sought.

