### **8.7.1 Statistical Analysis**

Assuming that all patients will have no response before vaccination, each patient will be classified as a responder or non-responder based upon an induration at the response site  $\geq 10$  mm. Fisher's exact test will be used to compare responses between groups after each vaccination.

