### **8.11.1 Statistical Analysis**

For laboratory screening tests of autoimmunity, any change from a normal to an abnormal value or a 2 fold change will be considered a positive result. A patient with any “positive” test will be considered positive and the number of positive tests will not be weighted. A 2 x 2 table will then be constructed to differentiate the frequency of positive patients by treatment group. A  $\chi^2$  test will then be used to assess if these frequencies are statistically significant.

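### The 80% power at 1.325σ that section 8.1.1 claims for every assay holds only for a single unadjusted two-sided t-test, not for the rank and binary comparisons planned in 8.5.1, 8.7.1 and 8.11.1

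*Protocol*

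**What the plan says.** Protocol section 8.1.1 bases the sample size on the primary endpoint, TReg suppressive function. It describes all other analyses as exploratory and says that no power calculations are provided for them. The next sentence gives one all the same, for 10 patients per arm: "we will have 80% power to detect difference $>1.325\sigma$ between groups for each assay at $\alpha=0.05".

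The tests that section 8 names for these assays are not all of one kind:

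- **Unpaired or two-sided t-tests:** TReg counts (8.3.1), cytokines (8.4.1), activation-induced cell death (8.6.1), proliferation and cytokine secretion (8.8.1), serology (8.9.1) and EGFRvIII PCR (8.12.1).
- **Rank test:** in 8.5.1 the arms are "compared relative to the number of phenotypic markers observed post-vaccination for each antigen using a Wilcoxon rank sum test". A Fisher comparison of the proportion with at least 4 positive markers is added as further exploration.
- **Responder counts:** for DTH (8.7.1), patients are classed by a 10 mm induration cut and "Fisher's exact test will be used to compare responses between groups after each vaccination".
- **2 x 2 table:** for sub-clinical autoimmunity (8.11.1), any positive laboratory test makes the patient positive, and a chi-square "test will then be used to assess if these frequencies are statistically significant".

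Section 8.2.1 sets 0.05 as the level for the primary and other assays unless otherwise indicated. It then adds: "A Bonferroni correction will be used to control for the multiple comparisons".

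**The concern.** A single power figure is attached to every assay, but the assays are analysed by different tests, and a figure in σ units carries over only to comparisons of means of a continuous measure. The statement also sits uneasily with the sentence before it, which says that no such figures are provided.

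These assays serve the secondary objective on enhanced immune responses and on immunologic evidence of autoimmunity (section 2.2.2). Section 2.1 hypothesises that daclizumab will not induce autoimmunity, so a non-significant comparison there would agree with the hypothesis. A reader who trusts the 80% could give that null result, or a null DTH result, more weight than the planned test can support.

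**Working it through.** **Inputs.** 10 patients per arm, a difference of 1.325σ, α = 0.05 and 80% power (8.1.1). Normal data with common standard deviation σ (stated in 8.1.1 for the primary calculation). Two-sided testing (8.4.1, 8.8.1, 8.9.1, 8.12.1).

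**1. The plan's own figure.** For a two-sample t-test with n = 10 per arm, df = 2 × 10 − 2 = 18. The noncentrality is 1.325 × √(10/2) = 2.963, and the two-sided critical value at 0.05 is 2.101. The noncentral t distribution gives power 80.0%, and the difference detectable with 80% power is 1.325σ. The figure is reproduced. Other formulas do not reproduce it: a one-sided t-test gives 88.6%, and a two-sided normal approximation gives 84.2%. So 1.325σ belongs to one two-sided t-test at an unadjusted 0.05.

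**2. Wilcoxon (8.5.1).** Simulation used normal data shifted by 1.325σ, 200,000 trials, and the exact critical value (U ≤ 23 or ≥ 77, actual level 0.043). Power is 75.5%. If the data are tied counts on six levels, closer to a count of positive markers, power is about 73% to 74%. Neither figure includes any correction across antigens.

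**3. Binary comparisons (8.5.1, 8.7.1, 8.11.1).** σ has no meaning for a proportion, so a model has to be assumed. The one used here cuts a normal measure at a threshold: if the lower arm has positive rate p0, the other has p1 = Φ(Φ⁻¹(p0) + 1.325). All 10 vs 10 tables were enumerated.

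| p0 | p1 | Fisher | Chi-square, uncorrected |
|---|---|---|---|
| 5% | 37.5% | 19.5% | 37.3% |
| 10% | 51.7% | 32.4% | 50.4% |
| 20% | 68.6% | 39.8% | 59.3% |
| 25.4% | 74.6% | 40.6% (maximum) | 60.4% (maximum) |
| 40% | 85.8% | 36.7% | 55.4% |
| 50% | 90.7% | 31.2% | 49.2% |
| 60% | 94.3% | 22.3% | 40.4% |

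For rates placed symmetrically about 50%, 80% power needs about 16% vs 84% with Fisher's test (equivalent to a shift of 1.99σ) and about 20% vs 80% with chi-square (1.67σ).

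**4. Bonferroni, conditional.** If the sentence in 8.2.1 is meant to reach the other assays, the t-test in step 1 is run at 0.05/m. At 1.325σ, power is 63.0% for m = 3 and 49.1% for m = 7. The plan does not give m outside the PHA doses. Seven is an illustration taken from the cytokine panel ("custom BioRad Bio-Plex 7-plex", 8.4). If the sentence covers only the PHA doses, this step does not apply.

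**The case against.** The best defence is that the number itself is right and its reach is limited by its own terms. Section 8.1.1 introduces σ as the standard deviation of normally distributed measurements, so a reader could take the sentence as covering only assays of that kind. DTH is described as routine skin testing and autoimmunity as laboratory screening, so whether they count as assays here is arguable. The same section calls the remaining analyses exploratory.

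Part of this stands. The 80% is correct for each comparison that really is a single unadjusted two-sided t-test. The percentages for the binary tests depend on an assumed latent normal measure, which fits the autoimmunity endpoint poorly because positivity there means any one of many tests changing. The exploratory label also limits the consequence. It does not remove the error: the power statement follows the disclaimer with a contrasting turn and makes no exception, and 8.5.1 is plainly a laboratory assay with a rank test as its main comparison.

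Four stronger readings are tempting, and the protocol does not support them.

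- **The cytokine panels are certainly Bonferroni-corrected.** Section 8.1.1 ties the correction to the three non-zero PHA doses, and 8.4.1 and 8.8.1 mention none.
- **The autoimmunity test would miss a difference of this size more often than not.** On the model above, its power is about 49% to 60% for lower-arm rates from 10% to 50%. It falls below that only outside this range.
- **The plan gives false reassurance on safety.** The dose-limiting toxicity and stopping rules in 5.3 and 10.2 do not use this p-value.
- **Analysing induration in mm would restore DTH power to 75–80%.** That needs roughly normal data, and many readings near zero would lower it.

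**Conclusion.** The point holds as a misstatement of scope. The 1.325σ figure is arithmetically correct for one two-sided unpaired t-test, 10 vs 10, at an unadjusted 0.05, and is wrong as a statement about every assay. The shortfall is small for the rank test in 8.5.1, about 75% against 80% with normal data. For the binary comparisons the claim is undefined as written. Under the threshold model, power is at most 41% for Fisher and at most 60% for uncorrected chi-square. A further loss from Bonferroni correction is conditional on how 8.2.1 is read.

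The sample size, the primary analysis, the decision on further development and the safety rules are unaffected. What is at stake is the weight given to null results in the secondary immunologic and autoimmunity comparisons.

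**What to change.** In 8.1.1, limit the 1.325σ sentence to assays analysed by one two-sided unpaired t-test at an unadjusted 0.05, or delete it; deletion would also agree with the sentence before it. In 8.2.1, say whether the Bonferroni correction covers only the PHA doses or other assays as well, and if the latter, over how many comparisons.

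If sensitivity is to be stated for the binary comparisons, give it as proportions: with 10 per arm, 80% power needs about 16% vs 84% for Fisher's test and about 20% vs 80% for the chi-square test. In 8.11.1, report the difference between arms with an exact confidence interval, so that a non-significant result is not read as absence of autoimmunity. An added DTH analysis of induration in mm is optional and should carry no promised gain in power.

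The cost is a few lines of text, one interval from data already collected, and a less favourable stated sensitivity. No patients or procedures are added.
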